**Methods:**

This is a single-blinded, parallel-group randomized controlled trial (RCT). Eligible participants from three local nongovernmental organizations (NGOs) will be randomly divided into intervention groups and control groups in a ratio of 1:1. The participants in the intervention group will receive 6 weekly 90-min group-based sessions delivered through a face-to-face and online approach. The participants in the control group will receive brief education on dementia care with the same group size, duration, and frequency as the sessions in the intervention group. Immediately after the intervention and at the 6-month follow-up, caring stress and other outcomes will be assessed. Besides, a focus group interview will be conducted to identify the strengths, limitations, and therapeutic components of the intervention from their perspectives. For quantitative data, intention-to-treat analysis and Generalized Estimating Equations (GEE) will be used. For qualitative data, content analysis will be used.

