### The rationale for using a simplified version of mindfulness programme

Developing a more simplified and less intensive mindfulness program could be a viable solution. A recent review of the duration of mindfulness training showed there was no association between the number of in-class hours spent on mindfulness training and the psychological outcomes of various participants. This implied that a MBI program with a longer duration would not yield a more significant effect on the psychological outcomes of the participants after they had learnt and mastered the skills of mindfulness [23], suggesting that a original MBI program with a total of 27 training hours may not be necessary. A three-arm study conducted by Demarzo et al. also found that those who participated in either an eight or four sessions MBI demonstrated significant improvements in different psychological outcomes compared to the control (usual care) group at the 2 and 6 month follow-ups, with similar effect size (0.42 vs 0.45 in depression, 0.15 vs 0.13 in resilience, 0.46 vs 0.57 in anxiety) at the 6-month follow-up [24].

There are existing studies which adopted a less intensive MBI, and these studies seem to suggest a more positive finding regarding its feasibility and effectiveness for family caregivers of PWD. A 7-session group-based MBI program for family caregivers of PWD (total 14 h trainings) was carried out and evaluated in a RCT design [25]. Compared to the educational control group, the MBI group significantly reduced stress, depressive symptoms, and BPSD-related caregivers’ distress immediately after the program and 6-month after. The completion rate was over 83% and the attrition rate was only at 11.1%. Most caregivers could practice mindfulness 180 min per week. From the interviews of the same study, caregivers suggested a less intensive approach and a more flexible delivery mode can potentially lead to more widespread use of mindfulness in dementia caregiving.

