### Sample size

The sample size is estimated based on the primary outcome of our study (perceived stress). This proposed study will adopt a simplified version of mindfulness training that differs from the protocol in our prior RCT [25]. Therefore, after considering the effect size of 0.36 in the prior meta-analysis on cognitive behavioural interventions for reducing stress in family caregivers of PWD [29], we adopted a conservative medium effect size of 0.40, which is similar to the effect size of psychological and behavioural interventions suggested by Cohen, to detect the mean difference in stress reduction between the intervention and control groups [30]. Considering the 20% attrition rate at 6 months that we found in our prior study, a sample size of 290 family caregivers (145 per group) is needed to achieve 80% power at 5% significance level (Two-sided). 20 caregivers from the intervention group will be purposively sampled to join in a focus group with a group size of 4 to 5 dyads per group one week after the intervention. After the intervention, equal proportions of participants with different levels (e.g., high, moderate, and low) of stress reduction will be selected.

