### Data analysis

SPSS version 23.0 will be used to analyze the data. An intention-to-treat analysis will be adopted. The demographic data will be presented in the format of descriptive statistics. Normality assumptions for the variables will be checked using the Kolmogorov–Smirnov (KS) test. Independent sample T-test (two-tailed) or Chi-square test will be used to examine demographic and clinical profiles between the two study groups. Generalized estimating equations (GEE) will be used to examine the study outcomes between the intervention and control groups across the three time-points (T0, T1, and T2). The dependent variables will be the mean total scores of the psychological health outcomes in the GEE analysis. The group, time points, and group x time interaction will be the independent variables. The missing data will be estimated in the GEE model based on the maximum likelihood estimation. Since there were no known covariates in our previous study, this assessment of homogeneity will be to identify any potential covariance in the outcomes. The possible covariates, such as age, gender, level of education, compliance, and psychiatric comorbidity, will be entered as covariates in a secondary analysis. All data analyses will be conducted with two-tailed tests with a significance level of p < 0.05.

For the interview data, content analysis will be performed using QSR NVivo 11. All audio recordings of the interviews will be transcribed into Chinese by the RA and the transcriptions will be checked for accuracy by the PI. To ensure trustworthiness, the transcripts will be coded independently by two Cantonese-speaking researchers. They will then discuss the codes by grouping them into main and subcategories with the support of verbatim data. The subcategories will then be re-organized. A set of subcategories with supporting verbatim data will finally be generated to identify the major strengths and limitations of the interventions as well as the long-term and short-term impact on caregiving. Any disagreements between the two researchers will be resolved through discussion with the larger research team.

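### The missing-data rule gives GEE a maximum-likelihood property that it lacks, so it cannot be carried out as written; the size of any bias cannot be fixed from the article

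*Protocol article*

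**What the plan says.** In the protocol article, Data analysis, GEE is the only outcome model named, applied over baseline (T0), post-intervention (T1) and 6 months (T2). On the model terms: "The group, time points, and group x time interaction will be the independent variables". Other variables "will be entered as covariates in a secondary analysis", so the main model holds only group, time and their interaction. On the population: "An intention-to-treat analysis will be adopted". On missing data: "The missing data will be estimated in the GEE model based on the maximum likelihood estimation". The abstract repeats the pairing of intention-to-treat with GEE.

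The section names no working correlation, imputation, weighting or missingness assumption.

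The Sample size section plans for dropout: "Considering the 20% attrition rate at 6 months that we found in our prior study". The background section on the simplified programme gives 11.1% attrition for the 7-session trial that the Sample size section cites as the team's prior RCT.

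**The concern.** GEE solves moment-type estimating equations on the records that were observed. There is no likelihood to maximise, and no missing value is estimated along the way. The sentence therefore attaches to GEE a property of another class of models. This is a wrong statement about the only outcome model named, not a detail left to an analysis plan: no plan could implement it while keeping ordinary GEE.

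The distinction has consequences. A correctly specified likelihood model remains valid when dropout depends on scores already observed. Unweighted GEE carries a general guarantee only when dropout is completely at random or depends only on variables in the model, and stress at T1 is an outcome here, not a model covariate. Objective 1 covers stress over the 6-month follow-up, where most attrition is expected. Dropout that differs by arm is plausible: Table 1 gives the intervention arm regular home practice, such as a 45-minute body scan on 6 of 7 days in week 1, while the description of the control sessions mentions none. Placed next to the intention-to-treat statement, the sentence tells the reader that dropout has been dealt with when the named method does not ensure it.

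**Working it through.** **Inputs from the article.** 145 per arm, 290 in total; planned effect 0.40 SD; 20% attrition at 6 months; model with group, time and group x time.

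**Scale of missingness.** 0.20 x 145 = 29 per arm without T2, 58 of 290 in total, leaving 116 per arm.

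**The plan's own figure.** The stated inputs give n = 2 x (1.960 + 0.842)² / 0.40² = 98.1, so 99 per arm; 99 / 0.80 = 123.75, so 124 per arm and 248 in total, not 290. That is a separate matter, and nothing below depends on it.

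**Assumptions not in the article.** Scores have unit SD and are jointly normal. The true effect is -0.40 SD at T1 and T2. Dropout at T2 follows a logistic model in the T1 score, calibrated to 20% in each arm.

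**Why independence GEE is exposed.** With a saturated group x time model and an independence working correlation, GEE returns the observed cell means. If dropout in one arm depends on T1 with log odds ratio b per SD, the T2 mean in that arm shifts by

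bias = r x m, where m = E[Z(1 - p(Z))] / 0.80, p(z) = 1 / (1 + exp(-(a + bz))),

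with Z standard normal, r the T1-T2 correlation, and a chosen so that the average of p is 0.20.

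- b = 1: a = -1.65, m = -0.173. Bias is 0.5 x -0.173 = -0.087, 0.6 x -0.173 = -0.104, or 0.7 x -0.173 = -0.121.
- b = 0.5: m = -0.096. Bias is 0.5 x -0.096 = -0.048 to 0.7 x -0.096 = -0.067.
- Opposite slopes of 1 in the two arms, r = 0.6: 2 x -0.104 = -0.208.
- Opposite slopes of 0.7: m = -0.130. Bias is 2 x 0.5 x -0.130 = -0.130 to 2 x 0.7 x -0.130 = -0.182.
- Same slope in both arms: the shifts cancel, and the bias is 0.

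The sign depends on the arm. If high-stress participants leave the intervention arm, the benefit is exaggerated; if they leave the control arm, it is understated.

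**Simulation across working correlations.** 1,000,000 participants, correlations 0.6 (T0-T1), 0.5 (T0-T2) and 0.6 (T1-T2), slope 1 where dropout is informative. Entries are bias in SD for the group x T2 effect; simulation error is a few thousandths.

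| Dropout at T2 (20% per arm) | GEE independence | GEE exchangeable | GEE AR(1) | GEE unstructured | Likelihood |
|---|---|---|---|---|---|
| Completely at random | 0.002 | 0.003 | 0.003 | 0.003 | 0.003 |
| On T1, same in both arms | 0.002 | 0.003 | 0.003 | 0.003 | 0.003 |
| On T1, intervention arm only | -0.103 | -0.003 | 0.000 | -0.003 | 0.001 |
| On T1, opposite by arm | -0.211 | -0.014 | -0.009 | -0.019 | -0.003 |
| On unobserved T2, intervention arm only | -0.172 | -0.105 | -0.111 | -0.108 | -0.108 |

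The independence column agrees with the formula. As a share of the planned effect, 0.103 / 0.40 = 26% and 0.211 / 0.40 = 53%. With compound symmetry at 0.5 or 0.7, the same pattern holds: roughly 0.09 to 0.18 SD for independence, at most about 0.006 for exchangeable and about 0.011 for unstructured.

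**Lower attrition.** At 11.1% with b = 1 in one arm, m = -0.100, so independence GEE is off by 0.5 x 0.100 = 0.05 to 0.7 x 0.100 = 0.07 SD.

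**The case against.** The strongest reply is that the sentence is loosely worded and that the authors mean only that every available assessment enters the model. For a continuous score, GEE with a working correlation close to the truth gives nearly the same answer as a likelihood model under MAR, and the table bears this out: at most 0.019 SD. The article does not name a working correlation, which an article may leave to the analysis plan, so the large figures rest on one choice that the authors may not make. They also need dropout to differ between arms. No section reports dropout by arm or by stress level, and the control sessions match the intervention in format, duration, frequency and group size. The slopes and correlations are assumed, and attrition may be nearer 11.1%. The article never uses the term missing at random; that is inferred from the reference to maximum likelihood.

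All of this stands as a limit on the consequence. A reader might infer that the primary analysis is valid only if dropout is completely at random, or that the 6-month estimate will be materially biased. The documents support neither: the first states a general guarantee as if it were a necessary condition, and the second depends on an unstated working correlation and an undocumented dropout pattern.

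What the reply does not rescue is the sentence. Using all available records is not maximum-likelihood estimation of missing data, and independence is not excluded by the text either.

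**Conclusion.** The missing-data rule is wrong as written. It describes something GEE does not do, and it credits the primary analysis with a likelihood-type validity that unweighted GEE does not guarantee in general.

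The bias itself is undetermined. With 20% dropout at T2 that depends on T1 stress differently by arm, it is about 0.05 to 0.2 SD under independence and about 0 to 0.02 SD under a working correlation near the truth. With the same mechanism in both arms it is about 0. These ranges rest on assumed log odds ratios of 0.5 to 1 per SD and T1-T2 correlations of 0.5 to 0.7. If dropout depends on unobserved T2 stress, every method in the table is biased, the likelihood model included.

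This should be fixed, but it is not a fatal flaw: the error in the text is certain, while material harm to the estimate is possible and not shown.

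**What to change.** Delete the sentence and make the method match the claim, before any outcome data are examined by arm. Either of these does so:

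1. Replace GEE by a likelihood-based mixed model for repeated measures with group, time and group x time, an unstructured covariance and all available assessments.
2. Keep GEE, with multiple imputation by arm using the T0 and T1 scores (or inverse-probability weighting), and state a working correlation other than independence.

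In both cases, state that the analysis assumes data are missing at random given the observed scores. For option 1 the text could read: *Outcomes will be analysed with a linear mixed model for repeated measures including group, time and group x time, with unstructured covariance, using all available assessments. Inference assumes that missing outcomes are missing at random.*

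The 20% and 11.1% attrition figures should be reconciled, or their different sources explained. A delta-adjusted sensitivity analysis for T2 would address dropout on unobserved stress; it is optional and can be left to the analysis plan.

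The cost is revised wording and a little more analysis work. Data collection and sample size are unaffected.

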## Background

Dementia is a worldwide public health priority that currently affects over 50 million people around the world, the number is expected to increase to 152 million by 2050 [1]. Similarly, the number of dementia cases in Hong Kong is predicted to triple from 100,000 cases in 2009 to 300,000 in 2039 [2]. Dementia is a syndrome that features a progressive and irreversible decline in cognitive functioning. It impairs one’s independent functioning and affects one’s daily living [3]. Over 90% of patients with dementia (PWD) experienced a range of behavioural and psychological symptoms of dementia (BPSD) including wandering, depression, and agitation [4]. Family caregivers of PWD involve in multiple caregiving tasks, such as aiding everyday activities of PWD and managing their BPSD. They also need to balance these caregiving tasks with other demands, such as their own career and social events [5, 6]. The caregiving burden, uncertainty about the progression of the disease, and family conflicts contributed to a high level of caregiving stress in caregivers [7]. Such stress can last for a decade, or until the care recipients passes away. The prolonged and high levels of stress could also put caregivers’ physical health at risk, resulting in various problems such as insomnia, high blood pressure, poorer immune function, a higher risk of developing other psychological symptoms and cardiovascular events [8–10]. Consequently, the high level of stress and poor psychological health of the caregivers will further affect the dyadic relationship, which may worsen the BPSD of the PWD [11]. Reducing the stress experienced by family caregivers can improve their physical and psychological well-being, dyadic relationship, and build their resiliency to take care of their PWD for a longer period of time. Moreover, the social distancing restriction during COVID-19 led to the suspension and reduction of community-based, as well as home care services for PWD. PWD felt frustrated and expressed anger to caregivers for staying at home [12]. The mental well-being of the caregivers was significantly affected due to isolation and limited respite. A research reported that the pandemic further increased the caregiver of PWD’s stress and anxiety level, particularly for those caring for patients with severe dementia [13]. Thus, stress reduction for caregivers is not only recommended but an imperative, especially during the time of Covid-19 [14].

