### Study procedure

Participants will be recruited via convenience sampling. Potential participants will be referred to the research team from three community center which provides services to the PWD (Collaborators of the research team). An independent Research Assistant (RA) will screen for their eligibility to participate in this study. A written informed consent will be sought from all the participants after the study was explained and all questions were answered. Following this, the participants will be interviewed about their health-socio-demographic information and complete the baseline assessment. Upon completion of the baseline assessment, they will be randomly allocated into the intervention group and control group (described in random allocation).

Follow-up assessments will be conducted by an independent RA who is blinded to the group assessing immediately after the 6-week intervention (T1), and after the 6-month post-intervention (T2). Focus group interviews will be conducted by within one week after T1 and at the 6-month follow up (T2) by an independent senior research assistant who has received training in how to conduct semi-structured interviews. Each focus group will last for about 60 min.

To ensure the RA can act as an independent outcome assessor throughout the stud, he/she will receive prior training on all the outcome instruments and interview techniques. The RA training will be provided by the PI. It consists of role play and on-site assessment practice with different clinical vignettes. Prior to the start of the study and throughout the data collection period, the scores rated by the assessor and the RA will be compared. The inter/intra-rater reliabilities will be evaluated by intra-class correlations (ICC). An ICC > 0.9 will be considered as an acceptable level of reliability.

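### Covariates for the secondary adjusted GEE are to be sought with between-arm baseline tests, which cannot show prognosis; the named list is open and includes a post-randomisation variable

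*Protocol article*

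**What the plan says.** All of this is in the Data analysis section unless noted.

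- Baseline comparison: "Independent sample T-test (two-tailed) or Chi-square test will be used to examine demographic and clinical profiles between the two study groups".
- Its purpose: because the team's previous study had shown no covariates, "this assessment of homogeneity will be to identify any potential covariance in the outcomes". The between-arm tests are the only assessment of homogeneity described, so the sentence most naturally refers to them. I read covariance here as covariates.
- The next sentence names age, gender, education, compliance and psychiatric comorbidity as examples of possible covariates and says that they will be entered in a secondary analysis.
- The main model is a GEE over T0, T1 and T2 with group, time and their interaction, and no covariates.
- Under Study procedure, baseline precedes allocation: "Upon completion of the baseline assessment, they will be randomly allocated into the intervention group and control group".

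**The concern.** The stated aim is to find variables related to the outcomes, but the tool is a test of whether the two arms differ at baseline. Under sound randomisation that null hypothesis is true by design, and the p-value carries no information on whether the variable predicts perceived stress. A variable unrelated to stress can be picked up by chance. A strongly prognostic one can be passed over because its difference is not significant.

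An adjusted analysis is there to show that the main result is robust. If its covariates can be settled only after the arms have been compared, or are taken from an open list, a reader cannot rule out that they were chosen with the result in view. Compliance adds a separate problem. It is recorded during the programme (Level of mindfulness section), so it can itself be affected by allocation, and conditioning on it can distort the treatment effect.

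**Working it through.** The protocol gives no figure for covariate selection, so there is none to reproduce. The check asks what the tests can detect, and what adjustment would change in the planned model.

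**Inputs.** 145 per arm, target effect 0.40 SD and 20% attrition at 6 months (Sample size section), hence 145 x 0.8 = 116 per arm at T2. Two-tailed level 0.05 and the GEE terms (Data analysis section). Covariate-outcome correlations are not given, so those below are assumptions.

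**1. Chance flags.** With k independent baseline tests at 0.05, the probability of at least one significant result is 1 - 0.95^k:
- k = 5: 23%
- k = 10: 40%
- k = 15: 54%

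The protocol does not fix k, and baseline variables are correlated, so these figures only show the order of size. They are the same whether or not any variable is prognostic.

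**2. What is not flagged.** For a continuous variable the smallest standardised difference reaching significance is 1.96 x sqrt(2/145) = 0.23 SD. Anything smaller passes as homogeneous, however strongly the variable predicts stress.

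**3. Effect on the planned contrast, complete data.** The effect at T2 is the group x time term, that is, the difference between arms in change from T0. Add a baseline covariate X with constant coefficient c. In each arm it contributes c times that arm's mean of X at T0 and the same amount at T2. The change in each arm therefore contains c(mean X) - c(mean X) = 0, and so does the difference between arms, whatever the imbalance. Simulated GEE fits with 116 per arm, a covariate correlated 0.5 with outcome and an imbalance of z = 1.5 agree: in one run the T2 contrast was -0.1818 with SE 0.1364, both with and without the covariate.

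**4. About 20% missing at T2, exchangeable working correlation.** The SE moved from 0.1483 to 0.1478 in one example, (0.1483 - 0.1478)/0.1483 = 0.3%. The estimate moved by about 0.01 to 0.02 SD.

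**5. Where adjustment does matter.**
- Dropout related to prognosis. The T2 means rest on those still observed. If dropout depends on a prognostic covariate differently in the two arms, the covariate no longer cancels. In simulation the unadjusted T2 contrast was then biased by about 0.04 to 0.10 SD, which is 0.04/0.40 = 10% to 0.10/0.40 = 25% of the target. Fixed adjustment removed the bias, with covariate x time terms where the covariate predicts change. The size depends on the assumed strength of the dropout relation.
- A covariate that predicts change. If its coefficient is c0 at T0 and c2 at T2, an imbalance D contributes (c2 - c0) x D to the contrast. Only a covariate x time term takes this up, and it also improves precision.

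**6. Overall type I error.** A simplified single-time-point comparison with one covariate, adjusted only when its baseline test was significant (116 per arm, 20,000 runs), gave rejection rates under the null of 0.050, 0.044 and 0.039 for correlations of 0.3, 0.5 and 0.6. None shows inflation.

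**The case against.** The case on the other side is substantial.

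- Five covariates are named and are to be entered. No rule makes entry depend on a significant baseline test, and compliance could not have come from such a test. A reader might infer that chance imbalance alone chooses the model; the text does not say so. What remains is that the list is only illustrative and that its relation to the preceding sentence is not explained.
- Only a secondary analysis is touched. This stands in full.
- A reader might treat the effect as a single follow-up difference and infer that an unflagged imbalance shifts the primary estimate by a sizeable part of 0.40, raises its conditional error, or costs several points of power. The documents do not support this: the planned contrast is a difference in change from T0, and steps 3 and 4 show that a covariate main effect barely touches it.
- A reader might also infer that dementia severity is an established prognostic factor left out by mistake, because the Background reports greater pandemic stress "particularly for those caring for patients with severe dementia". That remark concerns pandemic stress and does not establish a predictor of change in this trial. Absence from a list of examples is not exclusion.
- A closed covariate list is often left to an analysis plan, and none is shown. That would excuse an open list on its own. It does not excuse a stated selection method that cannot do its job, or naming a post-randomisation variable as a covariate.

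**Conclusion.** The point holds in a limited form and is worth correcting. The protocol assigns to between-arm significance tests the task of finding covariates, which they cannot perform under randomisation. The covariate set of the secondary GEE is therefore open to the data, can omit prognostic variables and, as named, includes one that arises after allocation. The main analysis and its error rate are not compromised.

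The gain from a fixed list is protection against dropout related to prognosis (0.04 to 0.10 SD in the illustrative simulation), precision where a covariate predicts change, and less analyst discretion. It is not a large gain in power for the planned contrast. This rests on reading the homogeneity assessment as the between-arm tests, on the interaction being the estimate of interest, and on assumed covariate and dropout relations that the protocol does not quantify.

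**What to change.** - Present baseline characteristics by arm descriptively, without p-values.
- Delete the sentence that uses the homogeneity assessment to find covariates.
- Replace the illustrative list with a closed list of prognostic T0 covariates for the secondary GEE, for example caregiver age, gender, education, psychiatric comorbidity and T0 NPI-Q severity. Enter all of them whatever the balance, with covariate x time terms where change is expected to depend on them.
- Take compliance out of this list.

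Cost: about two sentences of wording, a few extra model parameters and loss of the baseline p-values. No new data are needed, and the sample size and main GEE stay as they are.

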### Control group (Education on dementia care)

The family caregivers in the control group will receive brief education on dementia care which consists of 6 weekly 90-min group sessions, which will be delivered through a face-to-face (1st, 2nd, and 6th sessions) and online approach (3rd, 4th, and 5th sessions), with the same duration frequency and group size as the sessions in the MBDCP. The contents of the education offered to the control group will include brief education sessions on dementia care, caregiving skills, and group sharing. The group will be led by a registered nurse with experience in dementia care or elderly care.

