### Level of mindfulness

Participants’ level of mindfulness will be assessed and served as a process indicator of this study as our program aims to reduce caregivers’ stress by enhancing their mindfulness level. The Chinese version of Five Facet Mindfulness Questionnaire-Short Form (FFMQ-SF) will be used [46]; FFMQ-SF is a 20-item questionnaire that measures the five facets of mindfulness: observing, describing and acting with awareness, nonjudging of and nonreactivity of inner experience. Items are scored in a 5-point Likert scale (from 1-Never to 5-Very often). The total score ranges from 20 to 100, with a higher score indicating a higher level of mindfulness. FFMQ-SF demonstrates good validity and reliability in both non-clinical and clinical population of Hong Kong Chinese [47].

Furthermore, participants will be asked to record the frequency and duration of their mindfulness practice once a week via the online platform. They will also be asked whether they had complied with the practice regime in the past 7 days, using a score ranging from 0 (Not complied at all) to 10 (Fully complied).

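### The secondary adjusted analysis lists compliance, which arises after randomisation, beside baseline covariates, so its group effect would not be an intention-to-treat effect; the main GEE is unaffected

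*Protocol article*

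**What the plan says.** The main model is set out in the Data analysis section: an intention-to-treat GEE over T0, T1 and T2, in which "The group, time points, and group x time interaction will be the independent variables". The same section then plans an adjusted analysis: "The possible covariates, such as age, gender, level of education, compliance, and psychiatric comorbidity, will be entered as covariates in a secondary analysis".

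That section does not define compliance. The only description is under Level of mindfulness, where participants are to "record the frequency and duration of their mindfulness practice once a week via the online platform" and, on a scale from 0 to 10, "They will also be asked whether they had complied with the practice regime in the past 7 days". The section opens by describing the mindfulness level as a measure that "served as a process indicator of this study as our program aims to reduce caregivers’ stress by enhancing their mindfulness level".

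On timing, the Study procedure section says: "Upon completion of the baseline assessment, they will be randomly allocated into the intervention group and control group". On the comparator, the Control group section lists "brief education sessions on dementia care, caregiving skills, and group sharing". Home practice appears only in Table 1, which describes the mindfulness programme (MBDCP).

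**The concern.** Adjusting for variables fixed before allocation leaves the randomised comparison intact. Adjusting for something that allocation itself changes does not. Age, gender, education and psychiatric comorbidity are of the first kind. Compliance with a practice regime is of the second: people practise because they were assigned to the programme, and practice is a means by which the programme is meant to lower stress. Holding it fixed removes whatever part of the effect runs through practice. It also compares people selected on behaviour after allocation.

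There is a practical problem as well. If education-arm participants have no rating, a complete-case model drops them and no group effect can be estimated. If they are coded 0, the covariate nearly duplicates the group indicator.

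At stake is how the adjusted result is read. Set beside the main analysis, a null or reversed adjusted coefficient could be taken as a failed robustness check even though the programme works.

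**Working it through.** The plan gives no figure for the adjusted analysis, so there is none to reproduce.

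**Inputs from the protocol article.** Sample size section: 145 per group, 20% attrition, effect 0.40 SD. Completers per arm: 145 × 0.80 = 116.

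**Assumed inputs (not in the documents).** Compliance is 0 in every control; in the MBDCP arm its mean is 6 and SD 2. The true effect is -0.40 SD. A share *s* of that effect runs through practice. Compliance correlates *r* with a prognostic factor that lowers stress by 0.3 SD per SD. One follow-up score is analysed by linear regression on group, with and without compliance (2,000 runs per setting).

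**Step 1: without compliance.** SE = √(2/116) = 0.13. Power is 86% by formula and 84-87% in simulation. The mean estimate is about -0.40.

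**Step 2: precision with compliance.** With 1:1 allocation, the between-arm variance of compliance is (6/2)² = 9 and the average within-arm variance is (4 + 0)/2 = 2. So R² with group = 9/11, the variance inflation factor is 1/(1 - 9/11) = 5.5, and the SE ratio is √5.5 = 2.35. The simulated SE is about 0.31 (0.31/0.13 ≈ 2.4).

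**Step 3: the coefficient.** Controls have no spread in compliance, so its slope comes from the MBDCP arm alone:

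slope = -0.40*s*/6 - 0.3 × 2*r*/4 = -0.40*s*/6 - 0.15*r*

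group coefficient = -0.40 - 6 × slope = -0.40 + 0.40*s* + 0.90*r*

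Simulated means, which agree with this formula to within 0.02:

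| Share through practice | *r* = 0 | *r* = 0.3 | *r* = 0.6 |
|---|---|---|---|
| 0% | -0.41 | -0.12 | +0.14 |
| 50% | -0.19 | +0.06 | +0.35 |
| 100% | 0.00 | +0.27 | +0.54 |

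In the *r* = 0 column the group effect is significant in 26%, 10% and 5% of runs.

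**Step 4: if both arms were rated.** Take means of 6 and 5, SD 2 in each arm. The between-arm variance is (1/2)² = 0.25 and the within-arm variance is 4. The variance inflation factor is 4.25/4 = 1.06 and the SE ratio is 1.03. The precision problem almost disappears, but compliance is still measured after allocation.

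**Limit of the check.** The scenario is a single follow-up comparison, not the three-occasion GEE. The article does not say how compliance would enter that model. If it varies over time (zero for all at T0), it acts on the group-by-time terms as above. If it is one constant value per person entered as a main effect only, it cancels from change since T0. With complete data the group-by-time contrast is then unchanged, and the distortion falls on the group term.

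**The case against.** The strongest reply is that little of the trial is exposed. Compliance enters only a secondary analysis, in a list introduced as possible covariates, and the main GEE does without it. That stands. A reader might infer that the trial's primary conclusion is at risk; the Data analysis section does not support that.

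Second, the article never says that compliance means mindfulness practice alone. The Level of mindfulness section speaks of participants without naming an arm, and the education arm also has six weekly sessions, so a measure covering both arms could exist in a fuller document. This stands in part. It would remove the near-collinearity and the loss of the control arm, but such a measure would still be post-randomisation.

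Third, the figures rest on assumed inputs. This also stands. Where practice carries none of the effect and compliance is unrelated to prognosis, the estimate is unbiased and only precision is lost. As noted under the working, a person-constant main effect would leave the group-by-time contrast alone when data are complete.

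Two stronger readings are tempting:

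- That adjustment could make a useless programme look beneficial. This would need compliance to track worse prognosis. The documents give no direction for that relation, and no setting run here showed it.
- That covariates are chosen by baseline t-tests and chi-square tests. The text says "this assessment of homogeneity will be to identify any potential covariance in the outcomes", which is unclear, and the next sentence names covariates without making their entry depend on a p-value.

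**Conclusion.** The point holds for the secondary adjusted analysis and no further. A variable that arises after randomisation, and as described lies on the causal path, is listed with baseline covariates. The resulting group effect would not be the intention-to-treat effect that the section adopts. That conclusion follows from the timing alone and needs no simulation.

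The size cannot be taken from the documents. Under the assumed scenario the cost ranges from lost precision alone to a null or reversed coefficient. The 2.4-fold SE depends almost entirely on setting controls to 0. The positive coefficients also require compliance to track better prognosis. This is a clear error in a stated analysis choice, of moderate weight because the main analysis is sound, and it is easily corrected.

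**What to change.** Delete compliance from the covariate list and restrict the adjusted model to the baseline variables already named: age, gender, education and psychiatric comorbidity. The T0 score should not simply be added, because T0 is already a response occasion in the GEE.

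Examine compliance separately, in one of two ways:

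- describe practice and outcome within the MBDCP arm, labelled as a non-randomised comparison; or
- run a complier-average or mediation analysis, if suitable adherence data are recorded and its assumptions are stated. The article describes no attendance record, so a definition based on sessions attended would first need confirmation that those data will exist. Defining compliers as those attending all three face-to-face sessions is also doubtful, since partial attenders, online sessions and home practice could all carry benefit.

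The core change is one word in the analysis text. It alters neither the design, the sample size nor the data collection. Only the optional complier analysis might call for an additional adherence record.
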